#### Cost-effectiveness analysis

In line with the main analysis, the primary outcome for the economic evaluation will be mean score on the ABS during PTA. Secondary outcomes for the economic evaluation will be FIM at hospital discharge and quality-adjusted life years to 3-month follow-up calculated using SF12-based Six-Dimensional Health State Short Form (SF6D) scores derived using recently published Australian weights [70]. Treatment effects with respect to the ABS and FIM will be estimated as for the main analysis. Treatment effects with respect to the SF6D index score and total quality-adjusted life years to 3-month follow-up will be estimated using one-part generalised linear models, controlling for SF6D index scores at pre-treatment and specifying appropriate variance and link functions [77].

Patient-level data on total cost during inpatient rehabilitation admission will be extracted from patient medical records to capture medication use, therapy hours, length of stay and special nursing care. Post-discharge health service utilisation will be estimated from patient/MTDM self-report (at 3-month follow-up) regarding use of primary care, prescription and over-the-counter medications, allied health care, community care and paid and unpaid home-help as reflected on the PDHSUQ. Productivity gains/losses will be estimated based on length of inpatient hospitalisation, FIM scores at discharge and MPAI-4 scores at 3-month follow-up. Given the likely structure of our data and the advice of Buntin and Zaslavsky [78], treatment effects with respect to total cost will be estimated using one-part generalised linear models with gamma variance function and a log link (rather than transformed ordinary least squares or two-part models), controlling for patient characteristics at pre-treatment.

Results will be expressed as (i) cost per point improvement on the ABS, (ii) cost per point improvement on the FIM, and (iii) cost per quality-adjusted life year gained. We will summarise sampling error and parameter uncertainty using the bootstrap acceptability method to calculate confidence intervals and generate cost-effectiveness acceptability curves [77].

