### Participant timeline

The participant timeline is displayed in Table 1 schedule of activities.

**Table 1 Tab1:** Schedule of activities

Study phase	Screening/consent	Baseline/randomisation	Treatment period (PTA)	Post-PTA	Discharge	Three-month follow-up
ACD/ MTDM identification	X					
Trial introduction	X					
MTDM consent	X					
Screening	X					
Participant consent				X		
Randomisation		X				
Demographics^a^		X		X		
Medical record^b^		X	X		X	
Medical information^c^		X	X	X		
Blood test(s)^d^		X	X	X		
WPTAS		X	X			
ABS		X	X	X	X	
Simpson-Angus Scale		X	X			
Administer treatment			X			
Treatment log			X			
AE monitoring^e^			X			
RAVLT				X		
SDMT				X		
SF-12				X	X	X
FIM				X	X	
MPAI-4						X
PDHSUQ						X

^a^Age, gender, years of education, marital status, pre-injury employment/study status, drug and alcohol history, psychiatric history

^b^One or more of date and cause of injury, Glasgow Coma Scale, PTA duration, imaging results, surgical intervention, other injuries, Injury Severity Score, therapy hours and number of sessions, special nursing care, medication details, number of patients on ward

^c^Weight, BP, HR, WC

^d^Assessing fasting lipids, fasting glucose, HBA1C, creatinine

^e^Respiratory issues, lethargy, nausea, vomiting, difficulty swallowing, constipation, urinary retention, dizziness, seizures

#### Baseline—day 0

Following eligibility confirmation and randomisation, the following information will be gathered from the participant’s medical record: baseline WPTAS and ABS, demographic information (age, gender, years of education, marital status, pre-injury employment/study status, drug and alcohol history and psychiatric history) and medical information (date and cause of injury, Glasgow Coma Scale score, PTA duration, imaging results, surgical intervention, other injuries, injury severity score, therapy hours, special nursing care and medication details). Pre-treatment measures of weight, blood pressure (BP), heart rate (HR) and waist circumference (WC) will be conducted by nursing staff. Blood tests assessing fasting lipids, fasting glucose, haemoglobin A1c (HBA1C) and creatinine will be conducted. The Simpson-Angus Scale (SAS; [49]) will be completed by the patient’s treating physiotherapist, in order to assess the presence of extrapyramidal symptoms.

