#### Post-PTA—3 days following emergence from PTA (or 6 months)

Study staff will be informed by ABI ward staff when participants emerge from PTA and treatment will be titrated down as appropriate. Participant consent will be sought as soon as possible following emergence from PTA. Study staff will ask the participant to provide any demographic information unable to be gained from their medical record. Post-PTA measures of weight, BP, HR, WC and blood tests assessing fasting lipids, fasting glucose, HBA1C and creatinine will be conducted. The ABS will be completed daily for 2 weeks following emergence from PTA. Cognitive performance will be measured using the Rey Auditory Verbal Learning Test (RAVLT; [50]) and Oral Symbol Digit Modalities Test (SDMT; [51]). Functional independence will be measured using the Functional Independence Measure (FIM; [52]) and the 12-Item Short Form Health Survey Version 2 (SF-12; [53, 54]). These measures will be completed within 2 weeks of emergence from PTA. If participants remain in PTA at 6 months, treatment will be ceased and measures of weight, BP, HR, WC and blood tests will be administered at this time point. Remaining measures corresponding to the post-PTA time point will be administered upon the participant’s emergence from PTA.

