#### Three-month post-discharge follow-up

Participants and their MTDM will be contacted at 3 months post-discharge via telephone. Participants will complete the SF-12, their MTDM will complete the Mayo Portland Adaptability Inventory-4 (MPAI-4; [55]) and both parties will complete the Post-Discharge Health Service Utilisation Questionnaire (PDHSUQ). These measures will be completed within 3 weeks of the calculated follow-up date.

The participant’s MTDM may not be in a position to answer the questions posited in the MPAI-4 and PDHSUQ (for example, if they live in different countries or do not have a close relationship). In such cases, researchers will ask the participant to nominate another party who the researchers may contact to gather this information. Participants will be thanked for their participation and debriefed, including answering of any questions they might have regarding the study.

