Total cost per patient to 3-month follow-up, calculated by combining standard unit costs [69] with patient-level data on health service utilisation to 3-month follow-up and estimates of productivity gains/losses. Health service utilisation will be estimated based on medical record indicated medication use, therapy hours, length of inpatient hospitalisation, special nursing care and PDHSUQ as completed by the patient and their MTDM at 3-month follow-up. Once again, data collection from the point of view of the MTDM at this time point aims to overcome difficulties associated with poor self-awareness and memory in TBI patients. The PDHSUQ has been designed for the purposes of this trial to assess participants’ post-discharge use of medications, allied health services, psychologists or counsellors, general practitioner visits, use of paid or unpaid carers and admissions to hospital. Productivity gains/losses will be estimated based on inpatient length of inpatient hospitalisation, FIM scores at discharge and MPAI-4 scores at 3-month follow-up.Incremental cost of olanzapine and environmental management versus placebo and environmental management, calculated per patient to 3-month follow-up as the (adjusted) difference between olanzapine and placebo groups’ mean total cost per patient to 3-month follow-up.Incremental cost per unit improvement on the ABS (mean daily ABS scores for olanzapine and placebo groups during PTA).Incremental cost per point improvement on the FIM between PTA emergence and hospital discharge (mean scores for olanzapine and placebo groups).Incremental cost per quality-adjusted life year gained (mean scores for olanzapine and placebo groups calculated using the SF-12 SF-6D utility index scores and derived using recently published Australian weights [70]).

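### The QALY model adjusts for a pre-treatment SF-6D that the schedule never collects; the economic horizon moves with length of stay, and FIM improvement is defined in two ways

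*Protocol article*

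**What the plan says.** Under Cost-effectiveness analysis, treatment effects on the SF-6D index and on total QALYs are to be estimated by generalised linear models "controlling for SF6D index scores at pre-treatment and specifying appropriate variance and link functions". The cost-effectiveness item under Secondary outcomes says that QALYs are "calculated using the SF-12 SF-6D utility index scores", so the SF-12 is the only source of utility.

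Table 1 marks the SF-12 in three columns: Post-PTA, Discharge and Three-month follow-up. The visit text agrees. The Baseline—day 0 list contains neither the SF-12 nor the FIM. Both first appear at the post-PTA assessment, of which the article says "These measures will be completed within 2 weeks of emergence from PTA". The last SF-12 is tied to discharge: "Participants and their MTDM will be contacted at 3 months post-discharge via telephone".

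Total cost and QALYs both run to that 3-month follow-up. On the FIM, Secondary outcomes defines the ratio as "Incremental cost per point improvement on the FIM between PTA emergence and hospital discharge", whereas the analysis section states: "Secondary outcomes for the economic evaluation will be FIM at hospital discharge and quality-adjusted life years to 3-month follow-up".

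**The concern.** An analysis plan written later can settle many modelling details, but it cannot supply a measurement that no visit collects. As written, the QALY model has no data for its named covariate. The natural improvisation is to treat the first available SF-12 as the starting value. That score is taken after the treatment period, so adjusting for it could remove part of the effect being estimated.

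The other two matters concern comparability. A horizon that ends 3 months after each patient's own discharge is not the same length for everyone, and the article lists length of stay among the outcomes olanzapine may alter. A FIM gain counted from PTA emergence starts after the drug has been given, so whatever olanzapine did to function during PTA is subtracted. Cost per QALY, cost per FIM point and the period over which total cost is summed are at stake.

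**Working it through.** **Plan's own figures.** The article gives no utility, expected length of stay or QALY difference, so there is no economic figure to reproduce. Its one design calculation reproduces: a two-sample t-test at effect size 0.80, power 0.80 and two-sided alpha 0.05 needs 25.52, hence 26 per group, and 26/0.90 = 28.9, hence 29. Nothing below depends on it.

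**1. The covariate, schedule against model.**

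| Time point | SF-12 | FIM |
|---|---|---|
| Baseline | no | no |
| Treatment period | no | no |
| Post-PTA | yes | yes |
| Discharge | yes | yes |
| 3 months after discharge | yes | no |

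The model needs an entry in the first row, and there is none. A missed tick in the table is unlikely. The article describes the SF-12 as the patient's own view of their health, describes patients in PTA as confused and unable to form new memories, and mentions no proxy version. A single utility assigned to everyone in PTA would be a constant and could not act as a covariate.

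**2. The horizon.** Time counted from treatment start = days to discharge + about 91. For assumed stays of 30, 60, 90 and 180 days after treatment start, this gives 121, 151, 181 and 271 days.

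If both arms have the same constant utility u and one arm stays d days longer within the counted period, the difference in total QALYs is u × d / 365.25 with no difference in health. Both u and d are assumptions.

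| Extra days d | u = 0.4 | u = 0.5 | u = 0.7 |
|---|---|---|---|
| 7 | 0.008 | 0.010 | 0.013 |
| 14 | 0.015 | 0.019 | 0.027 |
| 30 | 0.033 | 0.041 | 0.058 |

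For example, 0.5 × 30 / 365.25 = 0.041.

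**3. The FIM.** The difference in change equals the difference at discharge minus the difference at emergence. With hypothetical scores of 80 against 70 at emergence and 100 against 95 at discharge, the discharge comparison gives 100 − 95 = +5, and the change comparison gives (100 − 80) − (95 − 70) = −5. The two definitions are therefore not interchangeable and can differ in sign.

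**The case against.** The best reply is that these are matters of wording in a secondary evaluation. Groups are randomised, so dropping an uncollected covariate costs precision and does not by itself bias the comparison. Mean ABS, not the QALY, is the primary economic outcome. On the FIM, both the functional-independence outcome and the analysis section already use the discharge score. All of this stands. It limits the consequence but does not remove the contradiction on the SF-6D.

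Several stronger readings are tempting, and the article does not support them.

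- A reader might infer that prolonged PTA would be credited as QALYs gained. That needs a positive utility during PTA, and the article states neither such a value nor when accrual begins. If accrual starts at the first SF-12, days in PTA add nothing, and only the interval from emergence to discharge stretches the total.
- A reader might add PTA, stay and 3 months to obtain the horizon. The treated part of PTA lies within the inpatient stay, so that sum counts it twice.
- A reader might say that the artefact dwarfs any real effect. That depends on the number of days chosen. Against an assumed gain of 0.05 held for a quarter of a year (0.05 × 0.25 = 0.0125 QALY), break-even at utility 0.5 is 0.0125 × 365.25 / 0.5, about 9 extra days. Seven days falls below it and 30 days well above it.
- A reader might treat the extra cost of a longer stay as spurious. Those inpatient days are real costs. The difficulty is only that costs are summed over unequal periods.
- A reader might conclude that cost per FIM point will have the wrong sign. That could arise only if the Secondary outcomes definition were followed over the other two places.

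**Conclusion.** The first part is wrong as written: the pre-treatment SF-6D is named in the model and collected nowhere, and the earliest available score is post-treatment. This rests on the schedule and visit text alone and needs no assumption.

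The second part holds more narrowly. The horizon is anchored to discharge, which treatment may shift, so total QALYs can differ without any difference in health. The size is 0.008 to 0.058 QALY over 7 to 30 extra days and utilities of 0.4 to 0.7. All of these inputs are assumed, so the figures show what is possible and are not a forecast.

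The third part is an inconsistency between one definition and two others.

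The effect is confined to cost per QALY, cost per FIM point and the horizon for total cost. The primary ABS analysis and the sample size are untouched. This should be fixed, but it does not threaten the main conclusion of the trial.

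**What to change.** 1. Delete the pre-treatment SF-6D from the SF-6D and QALY models. Adjust instead for variables already recorded at baseline, such as ABS, WPTAS, age and injury severity, and name them before unblinding. The cost model in the same section already adjusts for pre-treatment patient characteristics, so the two could share one list. Do not use the post-PTA score as a baseline. This costs wording only.

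2. State when QALY accrual starts and set a common horizon from randomisation for QALYs, and for costs as far as the data allow. Give the unmeasured PTA period one stated utility, equal in both arms, and vary it in sensitivity analysis. The cost is some interpolation or extrapolation and one assumed utility. A short horizon such as 13 weeks is not free of difficulty. The follow-up contact has a 3-week window, so an early call after a short stay may fall before week 13. PTA treatment may last up to 6 months with no measured utility. The article does not say that the service-use questionnaire dates each use, so costs may not be separable at a chosen date.

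3. Bring the FIM definition under Secondary outcomes into line with the other two places by using FIM at discharge. This costs wording only.

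### Discharge FIM enters both the cost and the effect in the cost-per-FIM-point ratio, so that ratio partly reports an assumed money value per FIM point

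*Protocol article*

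**What the plan says.** All the relevant text is in the Protocol article, in the cost-effectiveness item of Secondary outcomes (item 9) and in Cost-effectiveness analysis.

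- Total cost per patient is "calculated by combining standard unit costs [69] with patient-level data on health service utilisation to 3-month follow-up and estimates of productivity gains/losses".
- On the productivity part, Cost-effectiveness analysis states: "Productivity gains/losses will be estimated based on length of inpatient hospitalisation, FIM scores at discharge and MPAI-4 scores at 3-month follow-up". Item 9 gives the same three inputs.
- The only incremental cost defined is the (adjusted) "difference between olanzapine and placebo groups’ mean total cost per patient to 3-month follow-up".
- One of the three reported results is "ii) cost per point improvement on the FIM".
- The FIM effect is defined twice. Cost-effectiveness analysis says "Secondary outcomes for the economic evaluation will be FIM at hospital discharge". Item 9 says "Incremental cost per point improvement on the FIM between PTA emergence and hospital discharge".
- Total cost is to be modelled with "one-part generalised linear models with gamma variance function and a log link", controlling for pre-treatment characteristics.

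Neither place takes the FIM-derived productivity out of the cost when the effect is FIM.

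**The concern.** A cost-effectiveness ratio is easiest to read when the cost and the effect are measured separately. Here part of the cost is a conversion of the effect measure into money. Employment appears in Table 1 only as pre-injury status, and the listed content of the PDHSUQ covers service use, carers and hospital admissions. Productivity is therefore modelled from length of stay and two function scores. A group difference in discharge FIM is priced once as a cost change and counted again as the effect.

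Counting productivity is not the issue. A reader of the published cost per FIM point could not separate the observed cost of a FIM point from the price the analyst attached to it. The acceptability curve for the same ratio would carry the same mixture.

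**Working it through.** The plan gives no figure for this ratio, for the value of a FIM point or for the expected cost or FIM differences, so there is nothing to reproduce. The values below are assumptions used only to show the mechanism.

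**Notation.** dC is the group difference in all costs other than FIM-derived productivity. dD is the group difference in FIM at discharge and dE the difference at PTA emergence. v is the assumed money value per discharge-FIM point.

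**Case A: effect is discharge FIM, valuation linear, costs additive.**

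Ratio = (dC - v × dD) / dD = dC/dD - v.

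With dC = 5,000 and dD = 5, the ratio without the FIM term is 5,000/5 = 1,000 per point. With it:

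- v = 100: (5,000 - 500)/5 = 900
- v = 500: (5,000 - 2,500)/5 = 500
- v = 1,000: (5,000 - 5,000)/5 = 0

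For the acceptability curve, net benefit at threshold L is L × dD - (dC - v × dD) = (L + v) × dD - dC. Under Case A, a curve labelled L is therefore the curve for the other costs at L + v.

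**Case B: effect is change from PTA emergence to discharge (item 9).** Only the discharge component is shared:

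Ratio = (dC - v × dD) / (dD - dE), so the shift is v × dD / (dD - dE).

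With dC = 5,000, v = 500 and dD = 5, the numerator with the term is 2,500:

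| dE | Ratio without term | Ratio with term | Shift |
|---|---|---|---|
| -2 | 5,000/7 = 714 | 2,500/7 = 357 | 357 |
| 0 | 5,000/5 = 1,000 | 2,500/5 = 500 | 500 |
| 2 | 5,000/3 = 1,667 | 2,500/3 = 833 | 833 |
| 4 | 5,000/1 = 5,000 | 2,500/1 = 2,500 | 2,500 |

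A non-zero dE is possible, because the emergence FIM is taken after the treatment period.

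**Case C: valuation not linear.** Under an assumed logistic valuation (40,000 in total, centred at FIM 100 with scale 8; FIM SD 12), the average shift ran from about 683 to 893 per point, depending on the FIM level. It is then only locally constant. The log-link gamma model with covariates is a further departure from Case A, since it does not split the adjusted cost difference into additive components.

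**Cost-effect correlation.** In 20,000 simulated trials of 26 per arm (FIM means 100 and 105, SD 12; other costs gamma with shape 4 and scale 20,000, independent of FIM; v = 500), including the term moved the correlation between the cost difference and the FIM difference from 0.00 to -0.15.

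**Direction.** With dC = 5,000, v = 500 and dD = +5, the term lowers olanzapine's incremental cost from 5,000 to 2,500. With dD = -5 it raises it from 5,000 to 7,500.

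**The case against.** **A net-cost reading is legitimate.** Subtracting the savings that follow from a health gain gives a net cost per unit of effect, and dC/dFIM - v is exactly that. It is double counting in the strict sense only if the decision-maker's willingness to pay per FIM point already includes productivity, and the article states no threshold. This stands. The productivity-inclusive ratio may be reported, but not as the only version.

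**The valuation is not stated.** Productivity rests on three inputs, and FIM might enter as a threshold or jointly with MPAI-4. How they combine is a detail that may be left to the analysis plan, and its absence is not criticised here. It does mean that no size can be fixed. What the article does fix is that discharge FIM feeds the cost and that this cost is divided by a FIM effect.

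**Stronger readings that the documents do not support.** A reader might infer three:

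- That the ratio moves by exactly v whatever the data show. This needs all the conditions of Case A, whereas item 9 uses a change score and the planned cost model has a log link.
- That the ratio is always too favourable to olanzapine. The direction follows the sign of the FIM difference, and the Discussion part of the Abstract leaves open an adverse impact on functional outcomes.
- That the bootstrap intervals and acceptability curve are invalid because cost and effect are correlated. A bootstrap that resamples each patient's cost and effect together carries that correlation. The problem is what the curve means, not its validity.

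**The scope is narrow.** Only the FIM-driven part of productivity is affected, in one of three ratios. The primary economic outcome is the ABS, and the QALY ratio uses SF-6D scores. This stands too.

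**Conclusion.** The point holds in limited form. As written, discharge FIM enters both parts of the cost-per-FIM-point ratio, and the article describes no version that separates them. The ratio and its acceptability curve therefore partly reflect an assumed money value per FIM point.

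The shift equals v per point only if the valuation is linear, costs are additive and the effect is discharge FIM. Otherwise it varies: from 357 to 2,500 at v = 500 across the change-score examples above. Because v, dC and the FIM differences are not in the documents, material importance cannot be established in advance. Primary efficacy, safety, the sample size and the other two ratios do not depend on this point. It is a low-cost improvement to one secondary economic result.

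**What to change.** In item 9 of Secondary outcomes and in Cost-effectiveness analysis:

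- For cost per FIM point, use a numerator that excludes FIM-derived productivity. The simplest choice is health-service cost only, from the components already listed: medication, therapy hours, length of stay, special nursing care and post-discharge use from the PDHSUQ.
- Report the productivity-inclusive ratio beside it as a scenario, with the valuation per FIM point stated.
- Leave the ABS and QALY ratios on the planned total cost.
- Use one definition of the FIM effect, either discharge score or change from PTA emergence, in both sections.

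No new data are needed. The cost is one extra cost total and a few lines of text. The drawback is that the main FIM ratio then has a narrower cost perspective than the other two, which should be said where the three are reported together.
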